### Randomization

An independent statistician will generate the randomization codes. Patients will be block randomized according to a random number generator in alternating block sizes of three and six. Allocation will be concealed in sequentially numbered, opaque, sealed envelopes. Randomization will be stratified by primary CVD admission (myocardial infarction, heart failure, atrial fibrillation, other ventricular or atrial arrhythmia, coronary revascularization intervention, symptomatic CHD including angina pectoris, and heart valve disease) to obtain approximately equal sample sizes in both groups.

### Transdiagnostic unified protocol intervention

The UP is a transdiagnostic cognitive-behavioral intervention explicitly designed to address the full range of emotional disorders (anxiety, depressive, and related disorders); this work is done by targeting core, underlying emotional processes that lead to the development and maintenance of symptoms across disorders. The UP is designed for weekly and face-to-face delivery over 12 to 18 sessions. The UP consists of eight modules: (1) enhancing motivation for change and treatment engagement, (2) facilitating better understanding of patients’ emotional experiences, (3) increasing present focused emotion awareness, (4) increasing cognitive flexibility, (5) identifying and preventing patterns of emotion avoidance and maladaptive EDBs, (6) increasing awareness and tolerance of emotion-related physical sensations, and (7) interoceptive and situation-based emotion-focused exposure, and (8) the final module is devoted to summarizing the relevant techniques attained and to developing relapse prevention strategies. A summary of the UP decision tree and intervention outline is shown in Table 1. A more complete description by Barlow et al. [53] can be found elsewhere regarding the development of the UP and long-term treatment outcomes. An experienced psychologist, who is trained in the UP and trained by the research team on CVDs, will deliver the intervention. In psychotherapy intervention trials, blinding of the study participants, therapists, and study coordinator is not possible. However, all other members of the research team will remain blinded. Intervention fidelity will be maintained by weekly supervision and monitored to determine if the UP requires modification in a larger trial among CVD patients.

**Table 1 Tab1:** A Description of the eight modules for the transdiagnostic unified protocol in the intervention group

		Transdiagnostic unified protocol
Module	Session	Content
1. Preliminary module	1	Focusing on enhancing motivation and readiness for change and treatment engagement
2. Psychoeducation	2	Educating patients on the nature of emotions and providing a framework for understanding their emotional experiences
3. Present focused awareness	3 – 4	Increasing present focused emotion awareness
4. Cognitive flexibility	5 – 7	Increasing cognitive flexibility
5. Emotion-driven behaviors	8 – 11	Identifying and preventing patterns of emotion avoidance and maladaptive emotion-driven behaviors
6. Emotion awareness and tolerance	12 - 15	Increasing awareness and tolerance of emotion-related physical sensations
7. Exposure	16 – 17	Interoceptive and situation-based emotion focused exposure
8. Summary	18 (or earlier if required)	Summarizing the relevant techniques attained and developing relapse prevention strategies.

### Enhanced usual care

Patients randomized to the EUC group will receive an education package delivered by the study coordinator consisting of the beyondblue™ fact sheet regarding anxiety, depression, and coronary heart disease [54]. Participants and their general physician will be informed of the baseline distress results and directed to available clinical services (psychologist or psychiatrist), advising participants to seek assistance for achieving mental wellbeing with the support of their general physician. This conforms to the National Heart Foundation of Australia’s™ guidelines [51, 55]. There are no restrictions on usual care.

### Standard of care

All participants will receive standard medical care for CVDs according to international guidelines regardless of the study’s allocation. Standard CVD care includes referral to cardiac rehabilitation, which includes a structured exercise regime, and education about CVD risk factors such as stress, dietary modifications and tobacco smoking cessation. All study participants are permitted to seek psychopharmacology, which will be monitored, from outside the study.

### Procedure

The potentially eligible patients are being identified at the hospital 1 to 4 days after their CVD admission by an authorized hospital staff member employed as a trial coordinator in the cardiology department. A pool of eligible participants will be determined by the trial coordinator’s review of cardiology admissions and medical records if required. In the first instance, persons will be approached on the hospital ward by the trial coordinator and provided with the study information sheet and an opportunity to discuss any aspects of the study with the trial coordinator. The potentially eligible patients are re-contacted by the study’s trial coordinator by letter and then telephone 2 to 8 weeks after their CVD admission. Eligible and consenting participants will provide written informed consent at the baseline appointment. Determination of the depression and anxiety thresholds will be made at baseline. Randomization and patient allocation to trial arms will take place by means of a random number generator prepared in advance by an independent statistician offsite. All participants undergo active monitoring for CVD events and mental well-being (PHQ-9 and GAD-7) through a scheduled phone call every 4 to 6 weeks after randomization. The numbers of eligible and successfully recruited patients will be monitored and discussed on a weekly basis between the CI and trial manager.

### Patient rated measures

Psychosocial outcomes will be assessed with a battery of fully validated measures at baseline, after the intervention completion (12 to 18 weeks) and during the 6-month follow-up period. The timing of assessments is shown in Table 2. The self-rated measures will be collected to provide the standard deviation of patient outcomes, which is necessary to perform a power calculation in a larger more definitive trial. Patient rates of alcohol and tobacco use, physical activity, and hospital readmissions will be collected to provide an estimate for a larger more definitive trial.

**Table 2 Tab2:** Assessment schedule for participants through the study

			Timing of assessment for all participants					
		Eligibility	Pre-random ization	4 weeks	8 weeks	12 weeks	18 weeks	6 months
Variable	Measure							
Inclusion criteria								
Depression	PHQ-9	✓		✓	✓	✓	✓	✓
Generalized anxiety	GAD-7	✓		✓	✓	✓	✓	✓
Psychiatric diagnosis	MINI	✓					✓	✓
Post-eligibility								
Anxiety severity	OASIS		✓				✓	✓
General stress	DASS-21		✓				✓	✓
QOL	SF-12		✓				✓	✓
CVD outcome	MACE						✓	✓
Physical activity	Exercise		✓				✓	✓
GATS	Tobacco		✓				✓	✓
AUDIT-C	Alcohol		✓				✓	✓
MOS SAS	Adherence		✓					
Psychiatric service, medication usage, satisfaction with care	Self-report, audit		✓				✓	✓

AUDIT-C, Alcohol Use Disorders Identification Test-Shortened Clinical Version; CVD, cardiovascular disease; DASS-21, Depression, Anxiety Stress Scales; GAD-7, Generalized Anxiety Disorder-7; GATS, Global Adult Tobacco Survey; MACE, major adverse cardiac event; MINI, MINI International Neuropsychiatric Interview; MOS SAS, Medical Outcomes Study Specific Adherence Scale; OASIS, Overall Anxiety Severity And Impairment Scale; PHQ-9, Patient Health Questionnaire-9; SF-12, Medical Outcomes Study Short Form-12; QOL, quality of life;

### Anxiety, depression and stress symptoms

Generalized anxiety symptoms will be measured by the 7-item Generalized Anxiety Disorder scale (GAD-7). The GAD-7 severity threshold for clinically relevant symptoms is a total GAD score ≥ 7 [52]. This questionnaire has favorable validity as a tool to identify depression and anxiety disorders in medical patients [52]. The Overall Anxiety and Severity Impairment Scale (OASIS) is a five-item brief measure of anxiety symptoms, avoidance, and severity used in a number of large RCTs [56]. Scores > 8 are indicative of severe anxiety. Depression symptoms will be measured by the 9-item Patient Health Questionnaire (PHQ-9). The PHQ-9 severity threshold for clinically relevant symptoms is a total PHQ score ≥ 10 [52]. Stress will be measured by the Depression, Anxiety and Stress Scales, a 21-item clinical measure commonly used in Australia, validated in adults to age 90 years [57, 58], and in previous studies in the cardiac surgery population [59, 60]. Mild distress for the Stress scale is > 8.

### Other rating scales

Quality of life will be assessed with the SF-12. The SF-12 is a commonly utilized and generalizable measure of QOL in CVD populations [61, 62]. Other behavioral factors such as smoking and alcohol use are pertinent to cardiovascular functioning and are likely to be EDBs targeted by the UP intervention. Lifetime and current tobacco use will be measured by items from the Global Adult Tobacco Survey [63]. Recent alcohol use will be measured by the Alcohol Use Disorders Identification Test-Shortened Clinical Version, which provides favorable sensitivity and specificity for the detection of problematic drinking [64]. The physical activity questions from the Australian National Health Surveys are used to classify participants as sedentary or having low, moderate, or high levels of physical activity calculated with metabolic equivalents [65].

### Psychiatric disorders

The MINI is a brief structured interview that will be performed by allocation-naïve assessors to determine the primary psychiatric diagnosis and remission at the end of the study [66, 67]. Assessment takes 20 to 40 minutes to complete and has been validated among cardiac patients [68].

### Medical and demographic data

Demographic, comorbidity and CVD condition data will be obtained via project-specific questions. A statewide hospital registry will be used to identify CVD and psychiatric hospital admissions at 6-month follow-up. Major CVD events include myocardial infarction, stroke, coronary revascularization, cardiac failure, and arrhythmia determined with relevant International Classification of Disease Criteria Codes I00-I99 [69]. Admissions for primary psychiatric causes include suicide attempt, deliberate self-harm, and panic disorder (International Classification of Disease Criteria Codes F00-F99) [69]. Electronic data linkage will be used to determine admissions, and adjudication of study outcomes will be performed by an independent panel of cardiologists, blinded to the randomization arm. Patient confidentiality will be maintained.

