### Planned statistical analysis

Data management is outlined elsewhere in our protocol. Comparisons between UP, EUC and the nonrandomized comparator cohort will be made at each follow-up time point on patient level of satisfaction with aspects of psychosocial care. We will evaluate whether screening, education, and support in EUC is a suitable alternative to UP. We will also monitor linkages with primary care to determine whether our suicide risk management strategy is viable when routine depression screening is implemented. These data will help inform the design and day-to-day running of a larger more definitive RCT. In terms of feasibility, we will also evaluate the recruitment eligibility, acceptance, and attrition rates, the length of time taken to recruit, and compliance with the psychosocial questionnaire battery.

In the total sample, incorporating the nonrandomized comparator cohort, the association between EDBs, physical activity, and medication adherence with readmission will be examined. Incident psychological distress and distress trajectories will be evaluated in multi-level models to provide a snapshot of different distress trajectories on each of the measures used in CHAMPS. The longitudinal changes in QOL will also be analyzed in the same manner as incident psychological distress and distress trajectories described above.

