### Ethical considerations

The study has been approved by Human Research Ethics Committee of The Queen Elizabeth Hospital (approval #HREC/15/TQEH47). Written informed consent will be obtained from the participants before inclusion. Study participants are free to withdraw from the study at any time. The study carries a suicide risk, and therefore, the patients’ levels of suicidal ideation will be monitored with the PHQ-9 (every 4 weeks). As in our real-world clinic, we will follow a protocol for managing suicidal intent and self-harm attempts [38]. An independent data monitoring board will monitor adverse events (cardiac, psychiatric, and other) and report these to the governing ethics board. No plans are made to audit the conduct of the trial until it is completed.

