## Abbreviations

CVD: cardiovascular disease
CHAMPS: Cardiovascular Health in Anxiety or Mood Problems Study
EDB: emotion-driven behavior
EUC: enhanced usual care
GAD: generalized anxiety disorder
MACE: major adverse cardiac event
MINI: MINI International Neuropsychiatric Interview
OASIS: Overall Anxiety Severity And Impairment Scale
PHQ: Patient Health Questionnaire
QOL: quality of life
UP: unified protocol

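### Death is not named among the major CVD events, which are found through admissions, so a death without a prior CVD admission may leave no trace in the MACE and readmission results

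*Protocol article*

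**What the plan says.** Table 2 of the protocol article lists MACE as the CVD outcome at 18 weeks and 6 months. The Abbreviations only expand the term ("MACE: major adverse cardiac event"). The components are given under Medical and demographic data: "Major CVD events include myocardial infarction, stroke, coronary revascularization, cardiac failure, and arrhythmia", "determined with relevant International Classification of Disease Criteria Codes I00-I99".

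The same section gives the source. "A statewide hospital registry will be used to identify CVD and psychiatric hospital admissions at 6-month follow-up", and "Electronic data linkage will be used to determine admissions, and adjudication of study outcomes will be performed by an independent panel of cardiologists", blinded to arm. No death registry or other source of vital status is named.

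Under Planned statistical analysis, for the total sample, "the association between EDBs, physical activity, and medication adherence with readmission will be examined". Death is not mentioned there as an outcome, a component, a reason for censoring or a competing event.

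Two other sections bear on whether a death would become known. Under Procedure, "All participants undergo active monitoring for CVD events and mental well-being (PHQ-9 and GAD-7) through a scheduled phone call every 4 to 6 weeks". Under Ethical considerations, "An independent data monitoring board will monitor adverse events (cardiac, psychiatric, and other) and report these to the governing ethics board".

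**The concern.** The article does not leave this endpoint wholly to another document. It fixes components, codes, source and adjudication, and among the components it does not name the most serious cardiac event. An outcome found through admissions cannot by itself register someone who dies at home. Unless a further rule is added, such a person has the same record as someone who stayed well: no admission and no event.

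Two results are exposed. One is the MACE and readmission rates; Patient rated measures says that readmissions are collected to supply estimates for a larger trial, and the Discussion looks to effects on CVD events in that trial. The other is the association of behaviours with readmission: if people with riskier behaviour die more often, some are removed from the chance of readmission, and the association is pulled down.

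Psychiatric admissions have the same gap. Ethical considerations acknowledges a suicide risk, yet a completed suicide outside hospital would appear in neither the CVD nor the psychiatric admission outcome.

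**Working it through.** **Plan's own figures.** The article gives no mortality, MACE rate, event count or power calculation, so there is no design figure to reproduce here. The one related sum, 50 randomized + 150 cohort = 200 (Proposed sample), is correct.

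**Reading the sections together.**

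| Section | What it covers | Is death an outcome? |
|---|---|---|
| Medical and demographic data | Event list, codes, registry, linkage, panel | Not named |
| Planned statistical analysis | Association with readmission | Not named |
| Procedure | Calls every 4 to 6 weeks for CVD events | Could be learned; not made an outcome |
| Ethical considerations | Board monitors adverse events | Could be learned; reported to the ethics board |

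No section says how a participant who dies outside hospital is classified.

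**How many participants.** Let p be the six-month risk of death outside hospital. It is assumed to be 0.5% to 3%, since the article gives no value. Expected deaths = n × p. Chance of at least one = 1 − (1 − p)^n.

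| p | Expected, n = 50 | At least one, n = 50 | Expected, n = 200 | At least one, n = 200 |
|---|---|---|---|---|
| 0.5% | 0.25 | 22% | 1 | 63% |
| 1% | 0.5 | 40% | 2 | 87% |
| 2% | 1.0 | 64% | 4 | 98% |
| 3% | 1.5 | 78% | 6 | 99.8% |

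If every one of these deaths were cardiovascular and had no earlier CVD admission, the MACE proportion in 200 would be too low by 1/200 = 0.5 to 6/200 = 3 percentage points. That is an upper reading, because some would have been readmitted first.

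**Effect on the association.** Assumed inputs: a risk behaviour raises readmission among survivors from 15% to 25% and triples mortality. Nobody is readmitted before dying, which is the worst case.

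- Ratio among survivors: 0.25 / 0.15 = 1.67.
- Mortality 1% v 3%: (0.25 × 0.97) / (0.15 × 0.99) = 0.2425 / 0.1485 = 1.63. Relative to 1.67 this is 0.97/0.99 = 0.980, about 2% lower.
- Mortality 3% v 9%: (0.25 × 0.91) / (0.15 × 0.97) = 0.2275 / 0.1455 = 1.56. Relative to 1.67 this is 0.91/0.97 = 0.938, about 6% lower.

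In equal groups these inputs mean overall mortality of 2% and 6%, above the 0.5% to 3% used for deaths outside hospital, so 2% to 6% is not a low estimate.

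For readmission or death under the same inputs:

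- Mortality 1% v 3%: (0.2425 + 0.03) / (0.1485 + 0.01) = 0.2725 / 0.1585 = 1.72.
- Mortality 3% v 9%: (0.2275 + 0.09) / (0.1455 + 0.03) = 0.3175 / 0.1755 = 1.81.

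**Against sampling error.** With an illustrative 100 v 100 split and 15 v 25 readmissions, the standard error of the log ratio is √(1/15 − 1/100 + 1/25 − 1/100) = 0.294. The 95% interval is exp(0.511 ± 1.96 × 0.294) = 0.94 to 2.97, far wider than a shift of 2% to 6%.

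**The case against.** The strongest reply is that the article states no rule under which a death counts as a good outcome. The readmission analysis is described in one clause, with no model, denominator or censoring rule, and those details commonly sit in a full protocol or analysis plan that is not shown. The event list opens with a word that need not be exhaustive. A fatal infarction is still an infarction within the stated codes, and a blinded panel adjudicates outcomes. Calls and adverse-event monitoring give other routes to learning of a death, and readmission is a legitimate outcome in its own right.

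Most of this stands, and it rules out several stronger readings that a reader might infer:

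- *Deaths are counted as event-free.* No section says so. A death could be adjudicated, censored or treated as missing.
- *The listed events are non-fatal by definition.* The article does not say non-fatal.
- *The registry is the only source, so deaths go unseen.* The calls and the monitoring board contradict this. The board also means that MACE is not the trial's safety mechanism.
- *All deaths are lost.* Assumed all-cause mortality of 2% to 6% would give 4 to 12 deaths in 200, but a death during or after a CVD readmission already has a captured event.
- *The gap between 1.56–1.63 and 1.72–1.81 is bias.* Most of it arises because the composite is a different quantity, with an assumed threefold mortality ratio added to it.

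What the reply does not remove is that the section that fixes components and source leaves death unnamed, and the analysis names readmission only. Learning of a death by telephone does not give it a place in either result. The exclusion of conditions likely to be fatal within a year limits deaths among the 50 randomized, but the cohort eligibility criteria do not repeat it for the other 150.

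**Conclusion.** The point holds as a minor one. As written, a participant who dies without a prior CVD admission may add no event to MACE or readmission and be indistinguishable from one who stayed well. Under an assumed 0.5% to 3% six-month mortality outside hospital, this concerns about 1 to 6 of 200 participants, and the rates carried forward would be modestly understated. The effect on the association is small, about 2% to 6% under the assumed inputs, and its direction depends on the assumption that riskier behaviour raises mortality. CVD events and readmissions are non-primary outcomes in a feasibility trial with no power calculation, and a fuller protocol may already settle the matter.

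**What to change.** - **Medical and demographic data:** state that cardiovascular death, adjudicated by the existing blinded panel, is a MACE component, and that all-cause death is recorded. Name the source of vital status: the scheduled calls and, if it can supply deaths, the data linkage.
- **Planned statistical analysis:** keep readmission as the outcome, treat death as a competing event, and add CVD readmission or death as an accompanying analysis.

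The cost is a few sentences. The calls, linkage and panel already exist, though someone must confirm whether the linkage returns deaths. The drawback is that a composite mixes causes, so its components should be shown separately.

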### Intervention acceptability and feasibility

Participants will be asked to rate how effective different mental health care treatments were. The questions will assess psychologist treatments (a component of CHAMPS) and outside treatments: specifically, psychiatrist, GP counselling, anti-depressant, anti-anxiety medications, and other areas of support.

### Stopping rules

If there are concerns about significant emerging psychiatric symptoms (for example, psychosis, mania or other serious mental health conditions) associated with risks to the participant or others, and particularly if the PHQ score is ≥ 20 or the PHQ-9 item 9 score ≥ 2, the Mental Health Triage will necessarily be contacted, or alternatively, referral to an emergency department will be undertaken if a risk is imminent and high. If significant symptoms or comorbidities (for example, psychosis, hypomania, or substance use) that do not meet the previous criteria emerge at any point during the study, the psychologist will stop the study protocol, treat these conditions and/or provide appropriate referral for psychiatric or drug and alcohol service review. Psychiatric referral should be considered if there are significant risk factors for self-harm or CBT resistance such as personality disorder, past self-harm attempts or treatment-resistant depression.

### Ethical considerations

The study has been approved by Human Research Ethics Committee of The Queen Elizabeth Hospital (approval #HREC/15/TQEH47). Written informed consent will be obtained from the participants before inclusion. Study participants are free to withdraw from the study at any time. The study carries a suicide risk, and therefore, the patients’ levels of suicidal ideation will be monitored with the PHQ-9 (every 4 weeks). As in our real-world clinic, we will follow a protocol for managing suicidal intent and self-harm attempts [38]. An independent data monitoring board will monitor adverse events (cardiac, psychiatric, and other) and report these to the governing ethics board. No plans are made to audit the conduct of the trial until it is completed.

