### Exclusion criteria

Exclusion criteria include the following:A psychosis or bipolar disorder diagnosis determined by medical history or randomization-naïve assessors.High suicide risk at psychiatric interview.Observed cognitive impairment or dementia impeding delivery of psychotherapy or ability to provide informed consent.Neurodegenerative condition (for example, Parkinson’s disease or multiple sclerosis)In receipt of GP, psychologist or psychiatrist counselling elsewhere.A diagnosis of drug and alcohol dependence or abuse determined by randomization-naïve assessors.Medical condition likely to be fatal within 1 year.

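### The article promises PHQ-9 suicide monitoring every 4 weeks, but its call rule and assessment table allow 6-week gaps after week 12

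*Protocol article*

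**What the plan says.** Three places in the protocol article give the timing of PHQ-9 monitoring.

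- **Ethical considerations** names suicide as a risk of the study and, for that reason, states that patients' "levels of suicidal ideation will be monitored with the PHQ-9 (every 4 weeks". No range is given.
- **Procedure** has all participants monitored for "mental well-being (PHQ-9 and GAD-7) through a scheduled phone call every 4 to 6 weeks after randomization".
- **Patient rated measures, Table 2** ("Assessment schedule for participants through the study") marks the PHQ-9 at eligibility, at weeks 4, 8, 12 and 18, and at 6 months. Nothing is marked between weeks 12 and 18, or between week 18 and 6 months.

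The **Stopping rules** section uses these readings. It names a PHQ score of 20 or more, or an item 9 score of 2 or more, as particular grounds on which "the Mental Health Triage will necessarily be contacted", unless imminent high risk calls for emergency referral instead.

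**The concern.** The safety commitment and the working schedule give different intervals for the same measurement. Staff who follow the call rule and Table 2 to the letter can leave 6 weeks between PHQ-9 readings and so miss what the Ethical considerations section promises. That section also plans no audit of trial conduct before completion, so a drift to 6-weekly calls might not be noticed early.

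The interval has a practical consequence: the numeric triage triggers cannot act until a PHQ-9 is taken. Participants enter with a diagnosed emotional disorder and a PHQ or GAD score above threshold, so the monitoring is not a formality.

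The exposure differs somewhat by arm. Enhanced usual care patients "will receive an education package delivered by the study coordinator", have their baseline results sent to their general physician, and are advised to seek help; no study therapist contact is described for them. For the unified protocol arm, "The UP is designed for weekly and face-to-face delivery over 12 to 18 sessions", so these patients may still see the psychologist up to week 18, although Table 2 schedules no PHQ-9 at the weekly sessions. Once the sessions end they are in the same position as the usual care arm.

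**Working it through.** **Inputs**

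- Promised interval: 4 weeks (Ethical considerations).
- Call interval: 4 to 6 weeks after randomization (Procedure).
- Fixed PHQ-9 time points: weeks 4, 8, 12, 18 and 6 months (Table 2).
- The article does not give 6 months in weeks. I take 24 and 26 weeks as the two main readings.

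**Step 1: Table 2 alone.** The gaps from randomization are 4, 4, 4, 6 and then 6 weeks (6 months = 24 weeks) or 8 weeks (26 weeks). The 4-week interval holds to week 12 and fails after it. With 26 weeks, the 8-week gap exceeds even the 6-week limit of the call rule, so that rule already requires one call between week 18 and 6 months.

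**Step 2: slowest contact pattern that satisfies both the call rule and Table 2**, counting Table 2 assessments as contacts. Excess time is the sum of (gap − 4) over gaps longer than 4 weeks.

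| 6 months taken as | Contact weeks | Gaps (weeks) | Excess over 4 weeks | Share of follow-up |
|---|---|---|---|---|
| 24 weeks | 4, 8, 12, 18, 24 | 4, 4, 4, 6, 6 | 2 + 2 = 4 | 4/24 = 16.7% |
| 26 weeks | 4, 8, 12, 18, 24, 26 | 4, 4, 4, 6, 6, 2 | 2 + 2 = 4 | 4/26 = 15.4% |

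**Step 3: Table 2 plus calls every 4 weeks.**

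| 6 months taken as | Contact weeks | Gaps (weeks) | Longest gap | Contacts added to step 2 |
|---|---|---|---|---|
| 24 weeks | 4, 8, 12, 16, 18, 20, 24 | 4, 4, 4, 4, 2, 2, 4 | 4 | 7 − 5 = 2 |
| 26 weeks | 4, 8, 12, 16, 18, 20, 24, 26 | 4, 4, 4, 4, 2, 2, 4, 2 | 4 | 8 − 6 = 2 |

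The excess falls to 0 weeks under either reading.

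**Step 4: intermediate case.** Calls every 5 weeks, run as a separate series alongside Table 2, give no gap above 4 weeks if 6 months is 24 weeks. If it is 26 weeks they give one 5-week gap (weeks 20 to 25), an excess of 1 week, 1/26 = 3.8%.

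**Step 5: a longer reading of follow-up.** If 6 months were counted from the end of an 18-week treatment (18 + 26 = 44 weeks), 6-weekly calls would leave five 6-week gaps after week 12. The excess would be 5 × 2 = 10 weeks, 10/44 = 22.7%.

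**The case against.** The best defence is that the three statements can all be met at once. Four weeks lies inside the 4-to-6-week window, Table 2 does not forbid extra calls, and the ethics statement is itself a commitment that can be read as narrowing the call rule for suicide monitoring. That is true, and a site calling every 4 weeks would satisfy everything. But neither the call rule nor the table asks for the 4-week end of the window, and the table shows 6 weeks straight after week 12.

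A second argument is that a journal article condenses a fuller protocol, which may fix the call windows. It may. That would excuse a missing detail, but here the intervals are printed and they differ. The point is confined to that.

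Third, two 6-week gaps are the extreme case; 5-weekly calls give little or no excess. This stands, and the 15% to 17% should be read as an upper figure for follow-up of 24 to 26 weeks.

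Fourth, other protections exist. "High suicide risk at psychiatric interview" is an exclusion. Escalation can follow from clinical concern without a PHQ-9 score. A protocol for managing suicidal intent and an independent data monitoring board are in place. These limit the harm, but none of them sets how often the PHQ-9 is taken.

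Finally, with 6 months at 26 weeks, contacts at weeks 4, 8, 12, 16, 18, 22 and 26 would keep every gap within 4 weeks for one added call rather than two. That is correct, and it makes the remedy cheaper if contacts need not follow a regular 4-weekly grid.

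**Conclusion.** The inconsistency is real and should be corrected. Following the call rule and Table 2 secures the promised 4-week interval only to week 12. After that, the latest reading can be more than 4 weeks old for up to 4 of 24 or 26 weeks (17% or 15%). The figure assumes that Table 2 assessments count as monitoring contacts, that follow-up ends at 24 or 26 weeks, and that every call after week 12 falls at the 6-week limit.

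The consequence is minor to moderate: a possible delay of up to 2 weeks, beyond the stated interval, before a numeric triage trigger can act. The mismatch between the printed intervals is certain; how often staff would actually run to 6 weeks cannot be known from the article. No estimate, sample size or error rate is affected.

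**What to change.** Change the Procedure section to PHQ-9 calls every 4 weeks after randomization. Add the corresponding contacts to Table 2: weeks 16 and 20, and week 24 if 6 months means 26 weeks. Keep the week-18 assessment as it is. If the ethics approval in fact allows 4 to 6 weeks, correct the Ethical considerations section to say so instead. Either way, Procedure, Table 2 and Ethical considerations should give one interval.

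Correcting the ethics statement costs only wording. The 4-weekly rule adds 2 calls per participant beyond the slowest compliant schedule, and none if calls are already made every 4 weeks:

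- 50 randomized patients: 0 to 2 × 50 = 100 calls. At an assumed 10 minutes each the upper end is 100 × 10/60 ≈ 17 hours (8 to 25 hours at 5 to 15 minutes).
- All 200 participants, if the comparator cohort is also called: 0 to 2 × 200 = 400 calls, ≈ 67 hours (33 to 100 hours).

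This is coordinator time over the whole study. The only other downside is slightly more contact with participants, equal in both arms. The trial is recruiting, so the change can still benefit patients.
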